## 6. METHODS

### 6.1 Study parameters/endpoints

#### 6.1.1 Selection parameters

For the selection assessment we will use the PANSS to see whether the patient's level of positive symptoms is not too high for participation (see 3.3 Exclusion criteria and 5.1.1 main study parameters). To verify the DSM diagnosis and exclude alcohol and drugs dependence we will use the mini Schedules for Clinical Assessment in Neuropsychiatry (miniSCAN; WHO, 1992, 1999 vertaling Giel & Nienhuis 2000).

Table 3: other study parameters

| Parameter | Instrument | Duration   | Type                      |
|-----------|------------|------------|---------------------------|
| Symptoms  | PANSS      | minutes    | Semi structured interview |
| Diagnosis | MiniSCAN   | 30 minutes | Structured interview      |

### Positive and Negative Symptom Scale

The Positive and Negative Syndrome Scale (PANSS) is administered to monitor the changes in primary symptoms. The PANSS is a 30 item rating scale based on chart review and a semi-structured interview. It is widely used for assessing positive, negative and cognitive symptoms (Kay, Flszbein, & Opfer, 1987).

### MiniSCAN

The miniSCAN is a short version of the Schedule for Clinical Assessment in Neuropsychiatry (SCAN 2.1) and consists of a structured interview questions regarding axis-I symptoms of the DSM-IV (Damhuis, van Megen, Peeters, & Vollema, 2011).

#### 6.1.2 Main study parameters/end point

The main study parameters and subsequent instruments used in this study are shown in table 4.

Table 4: Main study parameters

| Parameter                         | Instrument                 | Duration   | Type                     |
|-----------------------------------|----------------------------|------------|--------------------------|
| Primary outcome measures   |                            |            |                          |
| Victimization                     | IVM                        | 10 minutes | Self-rating              |
|                                   | CTS2                       | 20 minutes | Self-rating              |
| Mediating factors          |                            |            |                          |
| Social cognition                  | Faux pas task              | 20 minutes | Neuropsychological task  |
|                                   | Wall of faces task**       | 20 minutes | fMRI task                |
|                                   | Emotional faces paradigm** | 15 minutes | fMRI task                |
| Self-expression and control       | ZECV                       | 10 minutes | Self-rating              |
| Internalised stigma               | ISMI                       | 15 minutes | Self-rating              |
| Social behavior                   | SIG                        | 15 minutes | Self-report              |
| Self-esteem                       | SERS-SF                    | 10 minutes | Self-rating              |
| Secondary outcome measures |                            |            |                          |
| Quality of life                   | MANSA                      | 5 minutes  | Self-rating              |
| Trauma                            | TSQ                        | 5 minutes  | Self-rating              |
| Recovery                          | NHS                        | 10 minutes | Self-rating              |
| Societal participation            | SFS                        | 20 minutes | Self-report              |
| Negative symptoms                 | BNSS in addition to PANSS  | 30 minutes | Semistructured interview |
| Fitness                           | MST                        | 15 minutes | Physical test            |
| Physical activity                 | Accelerometer              | 1 week     | Physical measure         |

\*IVM= Integrale Veiligheidsmonitor

CTS2= Revised Conflict Tactics Scale

ZECV= Self-Expression and Control Scale

ISMI= Internalized Stigma of Mental Illness

IOA= Inventarisatie Omgaan met Anderen

SERS-SF= Self-Esteem Rating Scale – Short Form

BNSS= Brief Negative Symptom Scale

MANSA= Manchester Short Assessment of Quality of Life

TSQ= Trauma Screening Questionnaire

NHS= Nationale herstelschaal

SFS= Social Functioning Scale

\*\* In case of participation in the MRI-substudy

### **Integrale Veiligheidsmonitor**

The Integrale Veiligheidsmonitor (IVM) is a Dutch crime and victimization survey that resembles the international crime victimization survey (CBS, 2009). We will use the victimization subscale (Victrom: Kamperman et al., 2014) and the subscales about safety perception in general and in one's neighborhood. Participants will complete the IVM pre- and post- treatment as well as during both follow up assessments, since we are particularly interested in victimization in the long term. The time-frame in the questions will be adapted, in order to investigate victimization between two subsequent assessment points. At baseline, the time-frame consists of the past five years. At both post assessments, victimization of past six months will be examined. At follow-up victimization of the past year will be assessed.

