They will be instructed to hand in the device at the following appointment. Patients who are also interested in participating in the MRI sub-study and meet the additional MRI criteria, are asked for a pretest MRI session. During this appointment of approximately 90 minutes participants will perform two tasks in an MRI scanner. After the pretest(s), participants will either receive the psychomotor assertiveness training consisting of 20 weekly training sessions (treatment-group) or befriending sessions (control-group). The last session, participants again receive an accelerometer. They will be instructed to hand in the device at the post assessment. Within two weeks after the last intervention session, a posttest assessment will take place. The appointment will take approximately 180 minutes. With patients who also participate in the MRI sub-study, a posttest MRI session will be planned. After six months, participants will be contacted again for a follow-up assessment consisting of questionnaires similar to the earlier pre- and posttest assessment. Respectively, a year and two years later, participants will be contacted for a second and third follow-up assessment. These assessments will take approximately 110 minutes and consists of an interview and questionnaires. More details about the selection and pre- and posttest instruments can be found in paragraph 5.1. Table 5 shows the study design of the instruments (see appendix F for instruments). The selection assessment, pre- and posttest assessments, follow-up assessments with questionnaires and the intervention sessions will take place at the mental health care institutions. The MRI sub-study will take place at the Neuroimaging Centre in Groningen.

Table 5: study design of the instruments

| Instruments                                      | Pre-selection | Selection | Pre-assessment | Post-assessment | Follow-up I | Follow-up II | Follow-up III |
|---------------------------------------------------------|----------------------|------------------|-----------------------|------------------------|--------------------|---------------------|----------------------|
| Selection criteria evaluated by onsite therapist        | x                    |                  |                       |                        |                    |                     |                      |

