| Positive and negative symptoms *(PANSS)                 |                      | x                |                       | x                      | x                  | x                   | x                    |
| Brief negative symptom scale * (BNSS)                   |                      | x                |                       | x                      | x                  | x                   | x                    |
| MiniSCAN                                                |                      | x                |                       |                        |                    |                     |                      |
| Integrale veiligheidsmonitor (IVM)                      |                      |                  | x                     | x                      | x                  | x                   | x                    |
| Revised Conflict Tactics Scale (CTS2)                   |                      |                  | x                     | x                      | x                  | x                   | x                    |
| Self-expression and control (ZECV)                      |                      |                  | x                     | x                      | x                  |                     |                      |
| Internalized stigma of mental illness (ISMI)            |                      |                  | x                     | x                      | x                  |                     |                      |
| Self-esteem rating scale – short form (SERS-SF)         |                      |                  | x                     | x                      | x                  |                     |                      |
| Screening Risico Verslavingsproblemen (Substance abuse) |                      |                  | x                     | x                      | x                  | x                   | x                    |

|                                                     |  |   |   |   |   |   |   |
|-----------------------------------------------------|--|---|---|---|---|---|---|
| Schaal Interpersoonlijk Gedrag (SIG)                |  |   | x | x | x |   |   |
| Faux pas task                                       |  |   | x | x | x |   |   |
| Wall of faces task**                                |  |   | x | x |   |   |   |
| Emotional faces paradigm**                          |  |   | x | x |   |   |   |

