### 8.2 Analysis

The effect of the training on long term victimization (primary study parameter) and on general long term outcomes, will be investigated by means of a repeated measures fixed-effects analysis of variance (ANOVA). The effect on risk factors of victimization (second study parameter) will be tested using multilevel modelling with the pre- and posttest and follow-up on the first level and training condition on the second level (o.a. Snijders & Bosker, 2000). A model will be constructed for every dependent variable and the dependent variables will be adjusted for covariates. Statistical analysis will be conducted using the IBM SPSS Statistics package. Dummy variables will be constructed for every level and the statistical significance of the regression-effects will be tested using the T-test. The dummy-variables and their interaction will be added to the model as fixed effects. The level of significance is set at  $p < 0.05$ , two-sided.

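### IVM recall windows of five years, six months and one year do not fit an unscaled repeated measures ANOVA; on the natural reading this costs power and interpretability, not validity between arms

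*Protocol*

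**What the plan says.** Table 4 in section 6.1.2 of the Protocol names two primary outcome instruments, the IVM and the CTS2. The IVM entry in that section sets the recall periods. For the pretest it states: "At baseline, the time-frame consists of the past five years". The period then shortens to six months for the two post assessments, and for the later visits it lengthens again: "At follow-up victimization of the past year will be assessed". The entry gives the purpose of the changing period as "in order to investigate victimization between two subsequent assessment points".

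Table 5 (section 6.3) schedules the IVM at five assessments. Section 3 describes one pretest, two posttests and two follow-ups. I therefore take the six-month window to apply to the post-assessment and follow-up I, and the one-year window to follow-ups II and III. On the first posttest, section 6.3 says: "Within two weeks after the last intervention session, a posttest assessment will take place".

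Section 8.2 says that the effect on long-term victimization "will be investigated by means of a repeated measures fixed-effects analysis of variance (ANOVA"). It does not say whether the IVM score is a count or any/none, whether it is scaled to the length of the window, or whether baseline is a level of the repeated factor or a covariate. Baseline IVM is not among the covariates in section 6.1.4. For the CTS2, the Protocol says only that items refer to a given period, and gives no length.

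**The concern.** A repeated measures ANOVA compares the same quantity over time. Here the quantity changes: at a constant risk, a five-year count is expected to be ten times a six-month count. If the five visits are levels of one repeated factor, part of any time effect is simply window length. The baseline visit also has by far the largest variance, and the group-by-time test must find the training effect against it.

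The Protocol fixes both the windows and the model, and the two do not fit, so this is more than detail left to an analysis plan. A second problem is that a window fixed at six months cannot serve the stated aim of covering the time between assessments unless that time happens to be six months. At stake is whether the primary comparison can detect a realistic effect, and whether incidents from before the pretest are counted again as outcomes.

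**Working it through.** **Inputs from the Protocol.** Windows of 5, 0.5, 0.5, 1 and 1 years (section 6.1.2). One-year prevalence of 47%, from the Dutch survey cited in section 1. Sixty per group with 25% drop-out (sample size section), so 60 × 0.75 = 45 completers per arm. That section gives no power for the section 8.2 ANOVA, so there is no plan figure to reproduce on this point.

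**Assumptions.** Incidents follow a Poisson or gamma-Poisson law with frailty variance φ = 0, 1 or 2. Each person's underlying rate is stable over time. The training halves the rate at every post-baseline visit (rate ratio 0.5).

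**Step 1: share of recall time.** 5 + 0.5 + 0.5 + 1 + 1 = 8 years, and baseline supplies 5/8 = 62.5%. At a constant rate the expected baseline count is 5/0.5 = 10 times a six-month count and 5/1 = 5 times a one-year count. In a total over all five visits, a true rate ratio of 0.50 appears as (5 + 3 × 0.50)/8 = 0.81.

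**Step 2: size of the variance mismatch.** The annual rate λ is set so that 47% have at least one incident in a year: λ = −ln(0.53) for φ = 0, otherwise λ = (0.53^−φ − 1)/φ. For a window of w years the mean is λw and the variance is λw + φ(λw)².

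| φ | λ | mean (SD), 6 months | mean (SD), 5 years | any incident, 6 months | any incident, 5 years |
|---|---|---|---|---|---|
| 0 | 0.635 | 0.32 (0.56) | 3.17 (1.78) | 27% | 96% |
| 1 | 0.887 | 0.44 (0.80) | 4.43 (4.91) | 31% | 82% |
| 2 | 1.280 | 0.64 (1.21) | 6.40 (9.40) | 34% | 73% |

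Risk is constant in every row; only the window changes.

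**Step 3: simulated rejection rates**, 45 per arm, two-sided 0.05. GG means Greenhouse-Geisser corrected.

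| Analysis | Rate ratio | φ = 0 | φ = 1 | φ = 2 |
|---|---|---|---|---|
| Group × time, raw counts, uncorrected | 1 | 0.078 | 0.107 | 0.110 |
| Group × time, raw counts, GG | 1 | 0.038 | 0.045 | 0.049 |
| Group × time, raw counts, GG | 0.5 | 0.103 | 0.063 | 0.051 |
| Same, with a one-year baseline | 0.5 | 0.280 | 0.324 | 0.374 |
| Group main effect, raw counts, all five visits | 0.5 | 0.551 | 0.145 | 0.099 |
| Group × time, any/none, GG | 0.5 | 0.246 | 0.210 | 0.177 |
| Same, with a one-year baseline | 0.5 | 0.231 | 0.194 | 0.176 |
| Post-baseline minus baseline, annualised rates | 0.5 | 0.798 | 0.857 | 0.907 |
| Post-baseline counts, no baseline | 0.5 | 0.966 | 0.727 | 0.517 |
| Post-baseline counts, baseline as covariate | 0.5 | 0.967 | 0.953 | 0.982 |

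Further runs with overdispersed counts gave uncorrected type I error of 0.09–0.12, GG power of 0.06–0.09, power of 0.27–0.40 with a one-year baseline, and 0.85–0.94 for pooled post-baseline counts adjusted for the five-year baseline.

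The long baseline window is therefore not the fault in itself. As a covariate, or as an annualised rate, it is informative. The damage comes from entering it unscaled as one more level of the outcome.

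**Step 4: the first post-test window.** Twenty weekly sessions run 19 weeks from first to last, or 20 if each is counted as a full week. Adding up to two weeks gives at most 21–22 weeks from the first session to the posttest. Six months is about 26 weeks. With the posttest at its latest, the window matches the interval since the pretest only if the wait from pretest to first session is 26 − 22 = 4 to 26 − 21 = 5 weeks. With the posttest straight after the last session, the wait would have to be 26 − 19 = 7 weeks. A shorter wait recounts incidents already in the five-year baseline; a longer one leaves a gap.

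**The case against.** The strongest reply is that section 8.2 never makes baseline a level of the repeated factor for the primary outcome. It names pretest, posttest and follow-up only for the risk-factor models. Since the text stresses long-term victimization, an ANOVA of follow-ups II and III alone, both with one-year windows, would have no mismatch. This stands as far as it goes: baseline as a level is an inference. It is still the natural one, because the design is pretest–posttest with follow-up, the IVM is collected at all five visits, and no passage gives baseline IVM another role.

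A reader might infer that unequal windows bias the comparison of arms. They do not. Both arms have the same window at each visit and both are offered 20 sessions, so the mismatch falls on the time effect. Nor is the error rate necessarily wrong: it is about 0.05 once sphericity is corrected, and the Protocol does not say that it would go uncorrected.

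A reader might also infer that the primary analysis has almost no power whatever is done. That holds only for the group-by-time test on raw counts with baseline as a level. The summary describes the two questionnaires as examining whether a person has been a victim, which fits any/none scoring. Group-by-time power is then low (0.18–0.25), but nearly the same with a one-year baseline (0.18–0.23), so the long window is not the cause.

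Finally, it is not established that incidents from before randomisation will be counted as outcomes. Neither the wait from pretest to first session nor the date of randomisation is given, and group start-up or an MRI pretest could fill the missing weeks. What stands is that a fixed window does not guarantee the coverage that section 6.1.2 aims for.

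**Conclusion.** The concern holds in a limited form. The stated IVM windows and the stated model do not fit, and no scaling is given. With baseline as a level and raw counts, the time effect is confounded with window length, sphericity fails, and group-by-time power is about 0.05–0.10 for a halved rate, against about 0.27–0.40 with a one-year baseline and 0.85–0.98 when the five-year baseline is a covariate for post-baseline counts. The loss is in power and interpretability; there is no bias between arms.

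These powers rest on the assumed rate ratio and overdispersion, on 45 completers per arm, and on individual rates that are stable over time. The last assumption favours covariate adjustment, so the gain would be smaller if rates drift. The mismatch is shown for the IVM only. The CTS2 window is unstated, so nothing follows about it beyond the need to specify one. The six-month coverage problem is real in principle, but its size depends on a wait that the Protocol does not give.

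**What to change.** 1. In section 8.2, model only the post-baseline IVM outcomes. Enter the five-year baseline IVM as a covariate in a form that allows zeros, such as log(count + 0.5), or any/none plus the count. A plain log rate is undefined for participants with no incidents, some 4–27% over five years by the table above.
2. In section 6.1.2, ask at each post-baseline visit about the period since the previous assessment, giving its date, and record both dates.
3. Analyse IVM incident counts with a count model, such as negative binomial, with log time covered as the offset.
4. For the CTS2, use the same since-last-assessment window and baseline as a covariate, but no count offset, because its items are scored in categories from 1 to 8.

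The cost is a changed question stem, a change of model for the IVM, and slightly more recall error where the interval turns out longer. If questionnaires with fixed windows are already in use, items 1 and 3 still apply, with the stated window (0.5 or 1 year) as the time covered.

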### **Revised Conflict Tactics Scale**

The revised Conflict Tactics Scale (CTS2) measures to what extent the respondent is involved in a psychological or physical attack and the use of reasoning or negotiation to deal with conflicts (Straus, Hamby, Boney-McCoy, & Sugarman, 1996). The CTS2 is a widely used instrument in partner violence research and consist of 39 behavior items. Participants report how many times, ranging from 1 'has never happened' to 8 'more than twenty times' the items apply on themselves or their partner in a given time period (Vega & O'Leary, 2007). Since we are interested in a broader range of social interactions we changed the questions from 'partner' to 'someone'. For example 'I kicked my partner' and 'My partner did this to me' is changed in 'I kicked someone' and 'Someone did this to me'. The CTS2 assesses more subtle forms of victimization, therefore this instrument is a good addition to the IVM.

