**Main study parameters/endpoints**

Primary study outcome is the long term effect of the psychomotor assertiveness training with elements of kickboxing on victimization, as measured by two questionnaires which examine whether an individual has been victim of a crime. We expect that this effect will be mediated by risk factors of victimization (e.g. social cognition, internal stigma, assertiveness, self-esteem, aggression regulation, social behaviour), as measured by both behavioural and cognitive measures such as interviews, questionnaires and a neuropsychological test, and cerebral measures such as fMRI paradigms. Secondary long term outcome measures are quality of life, recovery, social participation, negative symptoms and coping with trauma.

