### **5.1.1 Modules**

#### **Module 1 Introduction**

In the first module the participants will be introduced to each other and learn more about the session procedures. The exercises and information focuses on self-stigma, safety, respect for each other, and how to establish and set boundaries. In addition, participants will monitor the tension level in their body, during and after exercises, and learn how to reduce tension. All exercises are done with the help of six basic kickboxing punches and kicks, and a basic fighting stance.

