#### Module 2 Recognizing danger

The second module focuses on social cognition and insight. In addition to exercises from the first module that are repeated new exercises are offered regarding the recognition of emotion in facial expressions, prosody, and body language. Participants will learn the importance of considering other people's perspectives and how to verify their own. The techniques used in this module are blocking and deflection of the techniques learned in the first module. In addition, there are non-violent de-escalation techniques learned as an example of what a person could do in a threatening situation.

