#### Module 5 Repeat and combine

In the fifth module exercises and topics from previous modules are combined and repeated when necessary. Furthermore, participants are stimulated to continue martial arts in a regular

sporting gym. A guest trainer from a local fighting school is invited to give a lesson of 30 minutes, making the step to a regular school more accessible for the participants.

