### **7.2 Adverse events (AEs)**

None of the previous studies on exercise therapy or PMT, nor the feasibility study indicate any risk of adverse events. Furthermore, we do not foresee any problems caused by kickboxing. Although kickboxing is sometimes associated with aggression in the media there is no scientific prove that kickboxing itself induces aggressive behaviour. As shown in chapter 1 there are other explanations for the associated aggression. This is consistent with the findings of the pilot. In no way this training has been harmful for patients or for the people in their environment. Participants find the training enjoyable and experience a decrease rather than an increase in anger and aggression.

To prevent physical injuries, all exercises are carefully build-up during the training and participants can participate on their own physical level. It is possible that some participants will experience minor muscle aches after the training, especially those who are not used to physical exercise. Although participants learn how to be careful, adapt their kickboxing moves and use boxing gloves, shin guards and punching bags it is possible that someone will get a small bruise. Both the muscle ache and the bruise will disappeared in a few days and are not considered as health risks.

As shown in the exclusion criteria, in case of pregnancy, a participant cannot participate.

In case anything unforeseen happen, CCMO will be informed immediately. All adverse events reported spontaneously by the participant or observed by the investigator or his staff will be recorded.

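### The reworded CTS2, one of two primary instruments, states no exclusion of sport or training contact, so some training-arm respondents can report kickboxing practice as victimization

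*Protocol*

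**What the plan says.** The Summary (Main study parameters/endpoints) defines the primary outcome as the long-term effect of the training on victimization, "as measured by two questionnaires which examine whether an individual has been victim of a crime". Table 4 in section 6.1.2 lists these as the IVM and the CTS2, both self-rated.

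Section 6.1.2 (Revised Conflict Tactics Scale) explains the adaptation: "Since we are interested in a broader range of social interactions we changed the questions from 'partner' to 'someone". Its example, kicking, "is changed in 'I kicked someone' and 'Someone did this to me". Answers are frequencies on an eight-step scale whose top step is more than twenty occurrences. Neither this section nor any other part of the protocol tells respondents to leave out contact in sport, training or therapy.

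The training arm has 20 weekly group sessions and the control arm has befriending sessions (section 6.3). On the content of the training, section 5.1.1 says:
- Module 1: "All exercises are done with the help of six basic kickboxing punches and kicks, and a basic fighting stance".
- Module 2: "The techniques used in this module are blocking and deflection of the techniques learned in the first module".
- Module 5: "participants are stimulated to continue martial arts in a regular" gym.

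Section 7.2 mentions gloves, shin guards and punching bags, and accepts that "it is possible that someone will get a small bruise". Section 4.3 excludes people who currently take martial-arts classes. Table 5 schedules the CTS2 at the pre-assessment, the post-assessment and all three follow-ups.

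**The concern.** The partner wording limited who the other person was, and so largely in what setting an act could count. The adaptation removes that limit, and the protocol text puts nothing in its place. The act chosen as the example is one that the experimental treatment teaches. A respondent who reads the physical items literally can answer yes because of the sessions, although such contact is neither crime nor conflict and lies outside what the outcome is meant to capture.

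This is not noise shared by both arms. Martial-arts contact should be low in both arms at baseline because of the entry exclusion, and after randomisation it rises by design in one arm only. The resulting group-by-time difference is what the repeated measures ANOVA in section 8.2 would pick up. It could hide a real benefit or, if there is none, make the training look harmful. The perpetration half of each pair is open to the same error. That matters for interpretation because section 7.2 argues that the training does not increase aggression. Frequency answers collected without context cannot be separated afterwards.

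**Working it through.** **The plan's own figures.** The protocol gives no rate of training contact reported on the CTS2, so there is no figure to reproduce on this point. What follows is a reading of the timing and two illustrations.

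**Timing.** The post-assessment falls within two weeks of the last session (section 6.3). The recall window of the CTS2 is not stated. The IVM's window at the post assessments is six months, about 26 weeks. If the CTS2 follows it, 20 weeks of sessions plus up to 2 weeks is at most 22 weeks, so the first post-assessment covers the whole training. The next assessment comes six months later, so its window starts at about the post-assessment. From then on, exposure comes mainly from participants who continue martial arts.

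**Illustration 1: any physical report, yes or no.** Let C be the control rate, T the true training-arm rate, and p the share of otherwise negative training participants who endorse an item because of training contact.

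- Observed training rate = T + (1 − T) × p.
- The benefit vanishes at p* = (C − T) / (1 − T).

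The halving (T = C/2) is assumed. For C, the introduction's past-year rates are used as a range: 16% and 33% for violent crime, and 47% for any crime in a Dutch study of outpatients with severe mental illness. The 25% row is an assumed value inside the violent-crime range. None of these is a CTS2 rate.

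| C | T | p* |
|---|---|---|
| 16% | 8% | 0.08 / 0.92 = 8.7% |
| 25% | 12.5% | 0.125 / 0.875 = 14.3% |
| 33% | 16.5% | 0.165 / 0.835 = 19.8% |
| 47% | 23.5% | 0.235 / 0.765 = 30.7% |

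In the 25% row, p = 10% gives 0.125 + 0.875 × 0.10 = 21%, and p = 20% gives 0.125 + 0.875 × 0.20 = 30%. With no true effect and p = 20%, the training arm would show 0.25 + 0.75 × 0.20 = 40% against 25%.

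**Illustration 2: a continuous score.** The protocol plans 60 per group and 25% drop-out, which leaves 60 × 0.75 = 45 per group, and it assumes an effect of 0.50 SD. Let training contact shift the training-arm mean by b SD against the benefit. For a plain two-group comparison, power ≈ Φ((0.50 − b) / √(2/45) − 1.96), with √(2/45) = 0.211.

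| b | Power to show the benefit |
|---|---|
| 0 | 66% |
| 0.1 | 48% |
| 0.2 | 30% |
| 0.3 | 16% |
| 0.5 | 2.5% |

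The starting value is 66% and not the stated 80% because this simple comparison needs 63 completers per group, or 63 / 0.75 = 84 randomised. That is a separate matter. The value of b, like p, is assumed.

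**The case against.** The case against a stronger claim is substantial.

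- **The form has not been seen.** The instruments are in appendix F, and section 6.1.2 shows only one reworded pair. An instruction may already exist. What can be said is that the protocol text states none. This stands.
- **The conflict frame.** The scale is introduced as measuring attacks and ways of handling conflict, so many respondents may leave out consensual exercises unprompted. This stands: training contact can be reported by some, not by all.
- **Contact is implied, not stated.** A reader might infer that participants strike and bruise one another, and that 20 sessions would put them in the top frequency step. Blocking, shin guards and the foreseen bruises make partner work plausible. However, no section describes sparring, and punching bags are listed too. The documents do not support stating it as fact.
- **The primary outcome is long term.** If recall windows run between assessments, the sessions themselves fall mainly in the first post-assessment, and later waves depend on an unknown share who continue. This limits the effect on the primary question without removing it.
- **Only part of the outcome is exposed.** The IVM asks about crime, and the CTS2 also covers psychological attack and negotiation. Own aggression is not named as a primary outcome. All of this stands.
- **The yes/no illustration is loosely anchored.** It dichotomises a frequency scale and borrows crime rates for an instrument that the protocol says captures subtler events. The break-even moves from 8.7% to 30.7% with the control rate alone.

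These points limit how large and how certain the bias is. They do not supply the missing limit on the reworded items, and they do not make exposure equal between the arms. A control participant could take up martial arts later, but nothing in the design encourages it.

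**Conclusion.** The concern holds in a limited form. As the protocol text stands, the physical items of one of two primary instruments can take in contact that the treatment itself supplies, by design in one arm only. The direction is against the training. The effect should be greatest at the first post-assessment, and at later follow-ups it runs through those who continue martial arts. The IVM and the non-physical CTS2 items are largely unaffected.

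The size is unknown. With every input assumed, a true halving is cancelled when 14% of otherwise negative training participants endorse an item because of training contact (control rate 25%), or 31% (control rate 47%). On a continuous score, a shift of 0.1 to 0.3 SD would cut power from 66% to between 48% and 16%.

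A reader might infer that training kicks and punches necessarily count as violence throughout the training arm and that the primary result is therefore invalid. The documents do not support that: the rate of such answers is not given, the form is not shown, and half of the primary measurement is hardly touched.

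**What to change.** Check the adapted CTS2 in appendix F. If it already excludes sport and training contact, say so in section 6.1.2 where the rewording is described. If it does not, add one instruction sentence, for example: do not count contact that was part of a sport, a martial-arts class or a therapy or training session; report only acts that happened in a conflict or against the person's will. Use it in identical form in both arms, at every wave including baseline, and for both halves of each item pair.

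The cost is one line in a questionnaire that the trial already rewrites, with no added visit or staff and negligible time. The downside is small: a further departure from the published wording of the scale.
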